#### Follow-up visits

Participants will be followed at 1 month (visit 2), 3 months (visit 3), 6 months (visit 4), 9 months (visit 5), and 12 months (visit 6) after randomization. At each visit, the trial team will collect the information including incidence of foot ulcer, footwear adherence, cardiovascular events, glucose profile, and other cardiovascular risk factors control. For physical activity evaluation, participants will be asked to wear a pedometer (P084, SPORTWAY, ShenZhen, China) every day to record the date and steps taken per day. Meanwhile, a concealed activity monitor (Lifecorder Plus, Suzuken) will be attached to the diabetic therapeutic footwear. Activity data will be uploaded by a research assistant to a centralized server via internet at each follow-up visit. Adherence to treatment will be evaluated through the comparison of the step counts recorded by a concealed activity monitor with those recorded by a pedometer. Adherence to treatment will be monitored until the end of follow-up. Plantar pressure distribution patterns will be measured after randomization every 3 months. At the end of follow-up, ABI and blood flow parameters of lower extremities will also be collected. At each visit, if participants make a withdrawal request or are not eligible to continue due to the presence of severe concomitant diseases or conditions listed in the exclusion criteria, they will be discontinued from the study. For participants who drop out, the information including incidence of foot ulcer, footwear adherence, cardiovascular events, ABI (if possible), plantar pressures (if possible), and biochemical parameters (if possible) will be collected.

To improve participant retention and complete follow-up, the following measures will be adopted: participants’ contact information as well as contact information for at least two persons who would know the participants’ whereabouts and could get messages to them will be collected from the patients; a certain amount of subsidies (e.g., RMB 200) will be given to compensate participants for transportation and other costs at every follow-up visit; participants will receive phone appointment 1 day before every follow-up visit. If a participant could not be reached, a research assistant will make other appointments for the participant at least three times on different days, in an effort to schedule the site visit; a social networking platform (e.g., WeChat) will be used to connect with participants and then help investigators know participants’ condition in time, which will contribute to improve participants’ adherence and reduce lost to-follow-up.

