### Participants

Patients with a history of DFU whose healing time of foot ulcer was over 3 months will be invited to participate in our trial by phone. Individuals will be eligible for the trial if they meet the following inclusion criteria: (1) aged ≥ 18 years, (2) type 1 diabetes (T1DM) or type 2 diabetes (T2DM), (3) decrease or loss of protective foot sensation due to/as a result of diabetic peripheral neuropathy, and (4) had a healed foot ulceration in the 3 months prior to randomization. However, individuals will not be enrolled into this trial if they meet the following exclusion criteria: (1) amputation proximal to the tarsometatarsal joint, (2) the use of walking aids that offload the foot, (3) severe lower extremity artery disease (ankle brachial index ≤ 0.4, intermittent claudication or rest pain), (4) osteoarticular diseases unrelated to T1DM or T2DM, (5) decrease or loss of vision that is difficult to treat or correct, (6) unstable cardiovascular disease or unstable ischemic cerebrovascular disease, (7) severe renal dysfunction (estimated glomerular filtration rate (eGFR) < 30 mL/min per 1.73 m^2^) or severe liver dysfunction (Child-Pugh grade C), (8) malignant tumor, (9) severe illness that would make 24-month survival unlikely (as judged by the patients physician), (10) pregnancy or breast-feeding women, (11) neurologic or psychiatric disease that may prevent compliance with the protocol, and (12) patients who are considered unsuitable for the trial by investigators.

Potential participants will be given a brief verbal explanation of the trial by their treating podiatrist. Research assistants will give them telephone interviews and invite patients who are willing to participate to our diabetic foot center for further confirming eligibility and baseline measurements. Written informed consent will be obtained by a trained and experienced podiatric nurse or podiatrist at the baseline visit. On the consent form, participants will be asked whether they agree to use of their data and biological specimens when they choose to withdraw from the trial and asked for permission for the research team to share their relevant data with people from the universities taking part in the research or from the regulatory authorities.

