#### Secondary outcome measures

The secondary outcome measures include (1) the change of barefoot dynamic plantar pressures, from the third to the sixth diaries compared with that from the first diary (screening period); (2) the influence of footwear adherence on ulcer recurrence; and (3) the incidence of cardiovascular events.

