### Statistical analysis

At the end of this trial, all original data without participants’ name and the random sequences will be sent to a statistician for data analysis. Statistical analysis will be performed using SAS version 9.4 (SAS Institute Inc., Cary, NC, USA). Significance level will be set at *α* = 0.05. Quantitative variables expressed as means ± standard deviation or median with interquartile range, and categorical data will be recorded as numbers and percentages. Between-group differences of continuous variables will be tested for significance using Student *t* test when original data or data via transformation of variables is normally distributed or using Wilcoxon rank-sum test when data is not normally distributed. A chi-square test will be used for categorical data.

The primary end point, ulcer recurrence, will be analyzed according to the intention-to-treat principle, with event curves for the time to the first event on the basis of Kaplan–Meier analysis, and treatments will be compared by means of the log-rank test. A cox regression model will be used to calculate the hazard ratio for the primary end point. Among secondary end points, plantar pressures at baseline and at 3, 6, 9, and 12 months will be compared with repeated measures ANOVA. The changes blood flow parameters of lower extremity at baseline and at 12 months will be compared using Student *t* test when these means between groups are comparable at baseline or using analysis of covariance (ANCOVA) when these means are not equivalent at baseline. For cardiovascular events, the hazard ratio for the comparison of treatment group with control group and 95% confidence intervals will be estimated with the use of a proportional-hazards model.

The footwear adherence will be calculated for each group and then ulcer recurrence rates will be compared between the subgroups of patients with high adherence and low adherence by *χ*^2^ tests. We also plan to explore whether potentially important covariates such as age, sex, body mass index, physical activity, and diabetic duration could potentially confound the results.

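### Nothing keeps shoe wear recorded after the first ulcer out of the high/low adherence grouping, so the secondary adherence comparison can show protection that does not exist if wear falls after an ulcer

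*Protocol article*

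**What the plan says.** Follow-up visits (protocol article) defines adherence through the "comparison of the step counts recorded by a concealed activity monitor with those recorded by a pedometer". The monitor is described for one arm only: "a concealed activity monitor (Lifecorder Plus, Suzuken) will be attached to the diabetic therapeutic footwear". On duration, the same section says: "Adherence to treatment will be monitored until the end of follow-up". Some adherence information is also to be collected from participants who drop out.

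Statistical analysis says that adherence will be calculated for each group and that "ulcer recurrence rates will be compared between the subgroups of patients with high adherence and low adherence", using a chi-square test. It gives no cut-off and no time window for the adherence value that places a patient in a subgroup.

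Secondary outcome measures lists "the influence of footwear adherence on ulcer recurrence" as the second of three secondary outcomes, and the third objective includes the same question.

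**The concern.** A chi-square test on fixed subgroups gives each patient one adherence class and one yes/no outcome. It takes no account of which came first. The only time limit stated for adherence is the end of follow-up, and the primary endpoint is the first ulcer, so a patient who ulcerates in month 4 may have up to eight further months of adherence data. An active ulcer is not among the exclusion criteria, so it does not by itself end participation.

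If those later months enter the grouping and the share of steps in the shoe is lower in them, part of the low-adherence group is there because of the ulcer. The outcome then helps to set the exposure. Complete follow-up does not cure this.

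The Background and Discussion offer adherence as one explanation for earlier randomized trials that found no benefit. A spurious association here would look like confirmation.

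**Working it through.** The plan gives no figure for this comparison, so there is none to reproduce. The check asks what the stated test does when wear has no effect on ulcers.

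**Inputs from the protocol article**
- Footwear arm: n = 160 (Sample size calculation).
- Ulcer-free probability in the treatment group: 77.9%, so 12-month risk = 1 − 0.779 = 0.221. Expected ulcers: 160 × 0.221 = 35.4.
- Follow-up: 12 months, visits at 1, 3, 6, 9 and 12 months.

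**Assumptions (not in the documents)**
- Ulcer time is exponential and independent of wear.
- Pre-ulcer wear has mean 60% and SD 20% (set A), or follows Beta(3,2), Beta(6,2) or Beta(2,2) (set B).
- The high/low cut is the median; set B also uses 0.6 and 0.8.
- Wear after an ulcer is a multiple m of the patient's own earlier wear, varied below.
- There is no dropout.

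**Step 1. Effect on one patient.** Let a be the pre-ulcer share of steps in the shoe, t the month of the ulcer, m the multiplier on that share afterwards, and s the multiplier on total steps afterwards. Over 12 months:

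A = a × [t + s·m·(12 − t)] / [t + s·(12 − t)]

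With a = 0.60 and t = 6:
- m = 0.5, s = 1: 0.60 × (6 + 3)/12 = 0.45.
- m = 1, s = 0.3: 0.60 × 7.8/7.8 = 0.60. Walking less changes nothing.
- m = 0, s = 0.3: 0.60 × 6/7.8 = 0.46.

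The value falls only when the share falls (m < 1).

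**Step 2. The planned test with no true effect.** Uncorrected chi-square, median split, risk 0.221, 1,500 simulated trials per setting:

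| Wear after the ulcer | Recurrence, high vs low | False-positive rate |
|---|---|---|
| ×0.75 for 3 months (A) | – | 11% |
| ×0.5 for 3 months (A) | 17% vs 27% | 33% |
| ×0 for 3 months (A) | 12% vs 33% | 91% |
| Unchanged (B, Beta(3,2)) | 22.0% vs 22.1% | 4.2% |
| ×0.75 to month 12 (B, Beta(3,2)) | 16.6% vs 28.0% | 41% |
| ×0.5 to month 12 (A and B, Beta(3,2)) | 10% vs 34% | 96% |
| Same share, total steps ×0.3 (B, Beta(3,2)) | 22.4% vs 22.2% | 4.7% |
| ×0 to month 12, total steps ×0.3 (B, Beta(3,2)) | 10.7% vs 33.7% | 95.5% |

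**Step 3. Sensitivity.** With wear halved to month 12, the other cut-offs and wear distributions give risk ratios of 0.14 to 0.44 and false-positive rates of 33% to 100%. The lowest rate occurs when only 8% of patients fall in the high group. At a risk of 1 − 0.648 = 0.352 (the control-group assumption, used only as a higher value), ×0.75 to month 12 gives a risk ratio of 0.65 and 51%.

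**Step 4. Adherence taken only up to the first ulcer.** In set B the risk ratio is 0.98 to 1.02 and the false-positive rate 4.4% to 5.9%; in set A the rate is 4% to 6%.

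**The case against.** The strongest reply is that the sentence on duration concerns data collection. It says adherence is monitored to the end of follow-up, not that post-ulcer steps enter the grouping, and an analysis plan that is not shown could set the window. This stands as a limit on the point: a reader might infer that the protocol fixes a whole-follow-up split, and it does not. But the protocol does name the test and the fixed subgroups. That method does not order exposure and event in time, and the only endpoint given for adherence is the end of follow-up.

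Second, a reader might infer that an ulcer will push patients into the low-adherence group, so that a false result is almost certain. The documents do not support this. They say nothing about footwear use after an ulcer, and the fall in wear is an outside assumption.

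Third, rest is not a mechanism. The measure compares two step counts, and Step 1 shows that fewer steps at the same share leave it unchanged. This stands.

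Fourth, participants who "are not eligible to continue due to the presence of severe concomitant diseases or conditions listed in the exclusion criteria" are discontinued, and those criteria include "the use of walking aids that offload the foot". This could shorten post-ulcer monitoring in some patients. It is partial relief only: it does not define a pre-ulcer window, and adherence information is still collected from drop-outs.

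**Conclusion.** The point holds conditionally. As described, the adherence comparison does not protect itself against adherence that is a result of the ulcer. If post-ulcer steps are counted and the share of steps in the shoe falls after an ulcer, the test can report a protective association with no true effect. Under the stated assumptions the false-positive rate is about 11% for a mild, short fall (×0.75 for 3 months) and 96% when wear is halved to month 12. More extreme settings approach 100%. If the share does not change, or only pre-ulcer adherence is used, the rate is about 5%.

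The size therefore rests on a quantity that the documents do not give. The reach is limited to one non-randomized secondary comparison. The intention-to-treat log-rank and Cox analysis of the primary endpoint does not use adherence and is unaffected, as is the sample size. The point should be settled before analysis, because the comparison is a listed secondary outcome and the correction is cheap.

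**What to change.** In the footwear arm, replace the chi-square on fixed subgroups with a Cox model for first ulcer. Enter adherence (shoe-monitor steps divided by pedometer steps) as a continuous, time-dependent covariate, lagged to the preceding visit interval, so that no adherence data after the first ulcer are used. Add a landmark check: adherence to month 3 against first ulcers after month 3 in patients ulcer-free at that time.

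No new data should be needed. The pedometer records dated daily steps and activity data are uploaded at each visit. The article does not say that the shoe monitor is dated daily or that ulcer dates are finer than the visits, but visit-interval data are enough for the lagged covariate.

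The cost is in information. Under a constant hazard with 12-month risk 0.221, about 160 × (1 − 0.779^(1/12)) = 3.3 of the 35.4 expected ulcers fall before month 1 and have no lagged value. About 160 × (1 − 0.779^(3/12)) = 9.7 fall before the month-3 landmark, which leaves about 25.7 for that check, before dropout. The comparison also remains observational: patients who wear the shoe more may differ in other ways, and the report should say so.

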### Intervention

Two different types of footwear will be evaluated for feasibility and acceptability in this trial: optimally designed therapeutic footwear (Fig. 1) and usual care (patients’ own footwear for control group).

#### Optimally designed therapeutic footwear

Therapeutic footwear with merino wool, vibration chip, and orthopedic insoles will be optimally designed by the Beijing Ounce Health Technology Limited Company. The size of footwear will be defined based on patients’ foot size. Merino wool from New Zealand will be used for the manufacture of comfortable shoe vamp and lining. A Vibration chip is included in a Bloodstream Improvement Device (BID) which is designed to change external impact energy into vibration energy and placed at the back of the heel of therapeutic footwear. BID is a magnetic field generated by repulsive force that does not require any electric devices and can operate semi-permanently. The vibration of BID is natural penetration vibration penetrating deeply into the human body, which is a nature-friendly vibration different from other battery vibration. Orthopedic insoles will be designed and optimized using the footscan® system (RSscan international NV, Paal, Blegium). The insole will be constructed from merino wool and high-density polyurethane foam materials. Characteristics of orthopedic insoles and shoe soles were showed in Table 1.

**Table 1 Tab1:** Characteristics of orthopedic insoles and shoe soles of novel diabetic therapeutic footwear

Orthopedic insoles	
Rigidity	38 shore C hardness
Material	Polyurethane
Thickness of forefoot area	6 mm
Thickness of medial arch areas	12 mm
Thickness of lateral arch areas	8 mm
Thickness of heel area	6 mm
Shoe soles	
Thickness of forefoot area	12 mm
Heel height	23 mm
Midsole	
Rigidity	60 ± 3 shore C hardness
Material	Polyurethane
Specific gravity	0.9
Outsole	
Rigidity	60 ± 3 shore A hardness
Material	Rubber
Specific gravity	1.1
Thickness	4 mm
Depth of non-slip pattern	2.5 mm
Abrasion resistance	295 NBS
Tension resistance	142 kg/cm

#### Control footwear

The control group will receive patients’ own footwear. Control footwear will be constructed from materials commonly used in the manufacture of athletic shoes.

### Outcome measures

#### Primary outcome measure

The main study outcome measure is the incidence of ulcer recurrence. Ulcers are defined as cutaneous erosions through the dermis that may extend to involve the subcutaneous tissue or even to the level of muscle or bone [27, 28]. We expect at least a 30% reduction in the incidence of ulcer recurrence from baseline to the end of intervention.

#### Secondary outcome measures

The secondary outcome measures include (1) the change of barefoot dynamic plantar pressures, from the third to the sixth diaries compared with that from the first diary (screening period); (2) the influence of footwear adherence on ulcer recurrence; and (3) the incidence of cardiovascular events.

### Data management

All researchers including investigators, data collectors (i.e., research assistants), study coordinators, site monitors, data managers, outcome assessors, and a statistician will receive special training regarding the standard procedure and data management. During the recruitment period, data collectors will afford the collection of the baseline characteristics of participants and record them on study-specific CRFs. Data collectors will also collect and record the reports of laboratory findings and outcome measures on the CRFs during the recruitment or follow-up periods. Data will then be entered into Excel spreadsheets or EpiData manager by two collectors independently. Outcomes will be assessed by the principal investigator blind to intervention allocation during the study period. In the course of the trial, a data manager will be assigned to manage the relevant data. Researchers will assure that any personal information of participants collected remains strictly confidential. All data will be identified using participant numbers instead of directly displaying participant’s personal information. Access to the information will be restricted to the principal investigator or to researchers directly involved in the research at all times, before, during, and after the research activities. The data manager will check all data recorded on the CRFs and electronic documents after every visit and report back to the principal investigator and data collectors if there is any discrepancy. All data will be managed based on the Data Protection Act of 1998 [29]. All hard copy documents related to the research will be saved in a locked filing cabinet of Good Clinical Practice (GCP) Center of West China Hospital while electronic documents will be stored in a special computer with protected password. All research documents will be saved for at least 5 years after publication. If readers have any questions about our published data, they could contact our corresponding author (i.e., the principal investigator) to obtain the original data.

### Statistical analysis

At the end of this trial, all original data without participants’ name and the random sequences will be sent to a statistician for data analysis. Statistical analysis will be performed using SAS version 9.4 (SAS Institute Inc., Cary, NC, USA). Significance level will be set at *α* = 0.05. Quantitative variables expressed as means ± standard deviation or median with interquartile range, and categorical data will be recorded as numbers and percentages. Between-group differences of continuous variables will be tested for significance using Student *t* test when original data or data via transformation of variables is normally distributed or using Wilcoxon rank-sum test when data is not normally distributed. A chi-square test will be used for categorical data.

The primary end point, ulcer recurrence, will be analyzed according to the intention-to-treat principle, with event curves for the time to the first event on the basis of Kaplan–Meier analysis, and treatments will be compared by means of the log-rank test. A cox regression model will be used to calculate the hazard ratio for the primary end point. Among secondary end points, plantar pressures at baseline and at 3, 6, 9, and 12 months will be compared with repeated measures ANOVA. The changes blood flow parameters of lower extremity at baseline and at 12 months will be compared using Student *t* test when these means between groups are comparable at baseline or using analysis of covariance (ANCOVA) when these means are not equivalent at baseline. For cardiovascular events, the hazard ratio for the comparison of treatment group with control group and 95% confidence intervals will be estimated with the use of a proportional-hazards model.

The footwear adherence will be calculated for each group and then ulcer recurrence rates will be compared between the subgroups of patients with high adherence and low adherence by *χ*^2^ tests. We also plan to explore whether potentially important covariates such as age, sex, body mass index, physical activity, and diabetic duration could potentially confound the results.

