### Sample size calculation

PASS 11.0 software was used to obtain sample size. As a parallel-group randomized controlled trial, the Log-rank Test (Lakatos) was used for the sample size calculation based on the following parameters or assumptions:
The survival probability of treatment group was estimated for 77.9%. According to the latest national multicenter survey data in China, 31.6% patients with a history of DFU developed new ulcer during 1 year follow-up [5]. Thus, the survival probability of control group was assumed to be 64.8%. We assume that the treatment group could have a 30% higher survival probability than control group.The accrual period for patients’ recruitment was estimated for 12 months. The accrual pattern would be equal. The follow-up period would be 12 months. Therefore, the total time of this trial would last 24 months.The power was set at > 0.8, while *α* was 0.05. The dropout rate of 0.2 was assumed. No switching between two groups. Two groups would have same sample size.

Therefore, the total sample size calculated using PASS was at least 314 cases. In this trial, we would recruit a total of 320 patients (160 for each group).

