#### Baseline visit

After signing an informed consent, participants will be interviewed using a standard questionnaire to obtain information on demographic characteristics (including sex, date of birth, race, education, occupation, annual income, residence, family history and diabetic duration), lifestyle risk factors (physical activity, smoking status and alcohol consumption), history of past and present illness, and current medications. Blood pressure, height, weight and waist circumference will be measured with the use of standard methods. Fasting blood samples and urine sample will be collected to test blood routine, liver and renal function, eGFR, glucose, lipid, serum creatase, glycated hemoglobin (HbA1c), urine routine, and urinary albumin to creatinine ratio. Ankle brachial index (ABI) will also be measured using a pulse waveform analyzer BP-203RPE II (form PWV/ABI, Omron Healthcare Co., Kyoto, Japan).

Based on the above-mentioned information, eligible participants will be defined by an on-site investigator and then randomized to the study group or control group by an independent offsite investigator. Subsequently, every randomized participant will continue to perform plantar pressure tests by the trained podiatrist. Footscan® Pressure Measurement System (RSscan international NV, Paal, Blegium) will be used to obtain the data of plantar pressure. Before plantar pressures are measured, each participant will undertake at least two practice walks along the plate walkway to familiarize them with the experimental process. Then, each participant will be asked to walk in bare feet upon the footscan platform at self-selected gait speed for at least three successful trials. The foot data including peak plantar pressure will be recorded by the Footscan® pressure measure system, which automatically divided the foot into 10 masked regions: hallux, toes 2–5, first to fifth metatarsals, midfoot, medial heel, and lateral heel. Locations of previous ulceration, foot deformity or preulcerative signs will be the primary sites of interest. In additional, blood flow parameters of lower extremities, which include maximum systolic velocity, maximum diastolic velocity, and time-averaged mean velocity, will also be assessed by a vascular ultrasound specialist in the vascular ultrasound room of our hospital that is a quiet temperature-controlled environment. Measures will be performed at the same time of day for individual subjects.

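### The primary comparison names no covariates; a short list fixed in advance and measured before randomisation would give a modest, low-cost gain in precision

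*Protocol article*

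**What the plan says.** In the Statistical analysis section of the protocol article, the primary endpoint is analysed by intention to treat with Kaplan–Meier curves, and the arms are compared by the log-rank test. For the estimate, "A cox regression model will be used to calculate the hazard ratio for the primary end point". Neither the test nor the model is given strata or covariates.

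Covariates come in at the end of the section, where the investigators plan to explore whether "potentially important covariates such as age, sex, body mass index, physical activity, and diabetic duration could potentially confound the results". The list is introduced as a set of examples, so it is open.

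The Baseline visit section shows what is available. Before randomisation it records the questionnaire (including date of birth, diabetes duration and physical activity) and laboratory tests including HbA1c, and "Ankle brachial index (ABI) will also be measured". Eligibility is then decided and the patient is randomised. The plantar pressure test comes after that. Within that test, "Locations of previous ulceration, foot deformity or preulcerative signs will be the primary sites of interest".

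**The concern.** In a randomised trial, confounding is not the main reason to adjust for baseline variables, because randomisation already removes it in expectation. The reason is precision. In a Cox model, leaving out variables that predict the outcome moves the hazard ratio towards 1 and costs power. The plan gives covariates only the first role, in an exploratory step, and leaves the second unused.

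The exploratory list also omits ABI and HbA1c. The Background section itself treats arterial disease and reduced foot perfusion as contributors to ulcer risk.

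One listed item is ambiguous. Physical activity is in the baseline questionnaire, but the Follow-up visits section also measures it by pedometer after randomisation, when the footwear could affect it. An open list explored once the data are in also leaves some room for selective reporting.

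At stake is some power, in a trial that has less than its sample size section claims.

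**Working it through.** **1. The plan's own figure.** The inputs are in the Sample size calculation section: "The survival probability of treatment group was estimated for 77.9" (per cent), "the survival probability of control group was assumed to be 64.8" (per cent), and "The power was set at > 0.8, while *α* was 0.05". It adds 20% dropout, 12 months of uniform accrual and 24 months in total. Sidedness is not stated; two-sided is assumed here. A Lakatos log-rank calculation with these inputs gives N = 312 against the stated 314, so the figure is reproduced. Power at N = 320 is then 0.81.

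**2. Power with 12 months per participant.** Visits end 12 months after randomisation. The cited 31.6% recurrence implies control survival of 1 − 0.316 = 0.684, not 0.648. The value 0.779 matches 0.684, since 0.316 × 0.70 = 0.221 and 1 − 0.221 = 0.779.

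Take exponential hazards λ = −ln S and a dropout hazard δ = −ln 0.8 = 0.223. The probability of an observed event is λ/(λ+δ) × (1 − 0.8·S).

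- Treatment, S = 0.779, λ = 0.250: 0.199, so 160 × 0.199 = 31.8 events.
- Control, S = 0.684, λ = 0.380: 0.285, so 45.6 events; total about 77.
- Control, S = 0.648, λ = 0.434: 0.318, so 50.9 events; total about 83.

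The marginal hazard ratios are 0.250/0.380 = 0.658 and 0.250/0.434 = 0.576. Power is approximately Φ(√d × |ln HR|/2 − 1.96):

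- 68.4%: Φ(8.80 × 0.419/2 − 1.96) = Φ(−0.12) = 0.45 (Lakatos 0.45).
- 64.8%: Φ(9.10 × 0.552/2 − 1.96) = Φ(0.55) = 0.71 (Lakatos 0.70).

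**3. What adjustment adds.** The document gives no strength for any predictor. The assumed quantity is the SD of the baseline log-hazard score, taken from 0.3 to 1.0 (C-index about 0.58 to 0.74). Settings: N = 320, 12 months each, 20% dropout, marginal survivals held fixed, 1,000 simulated trials per row (Monte Carlo SE about 1.5 points). The last column puts the conditional hazard ratio and the same number of events into the formula of step 2, as a rough cross-check.

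| Control survival | SD | C-index | Conditional HR | Unadjusted | Adjusted | Gain (points) | Formula |
|---|---|---|---|---|---|---|---|
| 68.4% | 0.3 | 0.59 | 0.654 | 43.8% | 45.0% | 1.2 | 46% |
| 68.4% | 0.5 | 0.64 | 0.646 | 46.6% | 50.2% | 3.6 | 49% |
| 68.4% | 0.8 | 0.70 | 0.627 | 45.4% | 50.6% | 5.2 | 54% |
| 68.4% | 1.0 | 0.74 | 0.609 | 46.8% | 57.3% | 10.5 | 59% |
| 64.8% | 0.3 | 0.58 | 0.571 | 69.4% | 70.3% | 0.9 | 72% |
| 64.8% | 0.5 | 0.65 | 0.562 | 67.1% | 70.3% | 3.2 | 75% |
| 64.8% | 0.8 | 0.70 | 0.539 | 70.3% | 78.8% | 8.5 | 80% |
| 64.8% | 1.0 | 0.74 | 0.518 | 69.7% | 83.8% | 14.1 | 85% |

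A second simulation used 2,500 trials per setting, four standard-normal covariates, and SD 0, 0.5, 0.8 and 1.0. At 64.8% it gives adjusted power of 71%, 73%, 78% and 84% against about 70–72% unadjusted. At 68.4% it gives 44%, 47%, 53% and 60% against 43–48%. At SD 0, where the covariates carry no information, nothing is lost.

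**4. Can the model carry the covariates?** Treatment plus four single-parameter covariates is five parameters. With about 77 events that is 77/5, or about 15 events per parameter.

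**The case against.** The strongest reply is that nothing here is wrong. A log-rank test with a Cox hazard ratio, by intention to treat, is a standard analysis that keeps its type I error, and it matches the test on which the trial was sized. The text never calls the model unadjusted, and an article may leave the covariate set to a fuller document. That stands as far as it goes, and it is why this is not put as an error. It does not remove the point, because the article does give covariates a role, and that role is exploratory and framed as confounding.

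Four stronger readings might be inferred, and the document does not support them.

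- **That strong predictors are being ignored.** The Background and Discussion link plantar pressure and perfusion to ulcer risk, but give no strength of association with recurrence. Eligibility also narrows the range, since neuropathy is required and ABI of 0.4 or below is excluded. The simulations adjust for exactly the covariates that generate the risk, which is a best case.
- **That plantar pressure, deformity and pre-ulcerative signs are ready-made baseline covariates.** The Randomization and blinding section puts allocation after the baseline assessment, but the Baseline visit section expressly places the pressure test after randomisation. Deformity and pre-ulcerative signs appear there only as sites of interest for that test.
- **That adding covariates to the Cox model raises the power of the primary comparison.** That comparison is the log-rank test, which would be unchanged. The gain comes only if the adjusted Cox test becomes primary.
- **That the unadjusted hazard ratio is biased.** It estimates a marginal effect. Its distance from the adjusted value (0.658 against 0.627 at SD 0.8 and 68.4%) reflects two different estimands.

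The physical activity point is an ambiguity and no more. Its place beside age, sex and body mass index suggests that the baseline value is meant.

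**Conclusion.** The point holds as a recommended efficiency improvement. The planned analysis is valid but forgoes precision available from data already collected before randomisation. The gain is about 1 to 4 power points for SD up to 0.5 and about 5 to 14 for SD 0.8 to 1.0. These figures rest on assumed prognostic strength, exponential hazards, a two-sided 5% test and 20% dropout.

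It is not a remedy for the power shortfall. That comes from 64.8% versus 68.4% control survival and from 24 versus 12 months of follow-up, and must be dealt with separately. With 68.4% and 12 months, even the strongest assumed predictors reach only 57% to 60%, and 80% power for the log-rank test would need about 752 patients.

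**What to change.** In the Statistical analysis section:

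- Name as the primary treatment test and hazard ratio a Cox model with treatment plus a short list fixed in advance and measured before randomisation, for example age, diabetes duration, HbA1c and ABI.
- State that this test replaces the log-rank test as primary, and report the unadjusted log-rank and Cox results as supportive.
- If physical activity is used, take only the baseline questionnaire value.
- Leave out plantar pressure as scheduled. Use foot deformity or pre-ulcerative signs only if they are recorded before randomisation.

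The cost is a few lines of text, with no new data for the four example covariates. The change is still one of substance, because both the primary test and the estimand change: the adjusted hazard ratio is conditional on the covariates, so the unadjusted one must be shown with it. The choice should be fixed before any outcome data are seen.
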